**Neurocognitive testing***			
Declarative verbal memory (retrieval and recognition of VLMT)	X	X	
Cognitive processing speed and cognitive flexibility (TMT)	X	X	
Numerical short-term memory and working memory (Digit span backwards of WMS – R)	X	X	
Attention and concentration (d2 – R)	X	X	
Formal lexical and semantic verbal fluency (RWT)	X	X	

* Only for the intervention group

** Only for the control group

PCS Score, Post-COVID Score; PHQ-15, Patient Health Questionnaire-15; PHQ-9, Patient Health Questionnaire-9; GAD – 7, Generalized Anxiety Disorder Scale – 7; ISI, Insomnia Severity Index; FSS, Fatigue Severity Scale; PEM, Post-Exertional Malaise; ESSI, ENRICHD Social Support Instrument; SOC-3, Sense of Coherence Scale-3; PSS-4, Perceived Stress Scale-4; SSD-12, Somatic Symptom Disorder-12; PUK-2, Patient Competence in Coping with Cancer Questionnaire adapted for PASC symptoms; SF-36, Short Form Health Survey Questionnaire; VLMT, Verbal Learning and Memory Test; TMT, Trail Making Test; WMS-R, Wechsler Memory Scale-R; d2-R, Attention and Concentration Test; RWT, Regensburger Verbal Fluency Test

**Fig. 1 Fig1:**
[figure not shown]
Trial flow

### Participant’s eligibility and recruitment

Patients will be recruited from the Post-COVID Center at the Universitätsklinikum Erlangen. All study patients will receive comprehensive interdisciplinary diagnostics at the Post-COVID Center. After detailed information and consent, eligible patients will be allocated to either a control or intervention group.

#### Inclusion criteria

Aged 18 years or older.Confirmed (e.g. positive PCR or antigen test) SARS-CoV-2 infection and subsequent PASC: complaints that are still present more than 12 weeks after the onset of SARS-CoV-2 infection and cannot be explained otherwise.Written informed consent to participate in the study.Sufficient knowledge of the German language to participate in the study.Treatment group: indication for inpatient psychosomatic treatment due to:

Diagnosis of mental disorder (ICD-10; International Classification of Diseases, 10th Revision).Limitations that significantly reduce the ability to manage everyday life (e.g. the ability to maintain daily structure).and/ or

Subjective stress so great that the quality of life and everyday resilience are significantly limited.

6)Control group: depressive symptoms in self-assessment (PHQ-9 ≥ 10).

#### Exclusion criteria

Severely physically impaired patients (predominantly bedridden).Unique or main diagnosis of substance abuse (F10 – F19), schizophrenia, psychosis (F20 – F229) or organic psychiatric disorders (F00 – F09).Suicidality.Control group: utilization of PASC-specific outpatient or inpatient psychotherapeutic treatment or psychosomatic rehabilitation during 5 weeks of treatment.

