### Study design

This is a prospective non-randomized controlled trial. It is a two (group: intervention and control) by three (time: pre-treatment, 5 weeks, 6 months) repeated measures factorial design. The overall study design is illustrated in Fig. 1 and Table 1. In T0 sociodemographic data, medication, and use of previous psychotherapeutic inpatient or outpatient treatments, as well as data on health behavior (e.g. smoking, alcohol consumption, etc.) of the patients will be collected. Participants in the intervention group will complete a comprehensive web-based questionnaire battery at three time points: at the time of admission to the hospital setting (T0), at the end of inpatient treatment five weeks later (T1), and 6 months after discharge from the hospital setting (T2). The control group will accomplish the questionnaire within a time frame of around 6 months after presentation at the Post-COVID Center of the Universitätsklinikum Erlangen (T0), five weeks after T0 (T1), and 6 months after T0 (T2). The questionnaires at T0, T1, and T2 will be made available web-based via a link and a password. Participants who drop out of the intervention or control group will be reported in the final results. Before participation, written informed consent must be given. A schematic overview of the trial flow is given in Fig. 1. The instruments used at each time point are displayed in Table 1.

**Table 1 Tab1:** Overview of the assessment schedule for both groups

Measures	Assessment time points		
	Baseline (T0)	5 weeks later (T1)	6-month follow-up (T2)
Sociodemographic variables	X		
Health behavior	X	X	X
Use of PASC-specific treatments		X**	X
Use of PASC-specific outpatient or inpatient psychotherapeutic treatment	X	X**	X

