### Control group

The control group will consist of PASC patients for whom there is an indication for inpatient psychosomatic treatment (depressive symptoms in self-assessment: PHQ-9 ≥ 10), but who do not take up the treatment. After group allocation, participants in the TAU condition will have no access to the inpatient psychosomatic treatment, but will not be restrained from using any form of care for PASC-related symptoms. Treatment as usual for PASC patients can entail follow-up contacts with their treating physician or general practitioner, physical training, occupational therapy, or rehabilitation. At T0, T1, and T2, participants of the control group will be questioned about the received psychotherapeutic inpatient or outpatient treatment.

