**Fig. 2 Fig2:**
[figure not shown]
Four cornerstones of PASC specific inpatient psychosomatic treatment

**Medical treatment** Our comprehensive multidisciplinary medical assessment will include detailed medical examination at the beginning and end of treatment, with evaluations by specialists if new symptoms arise and weekly medical consultations.**Neurocognitive training** Neurocognitive training will be carried out independently with the digital health application NeuroNation MED [45] at least twice a week. The individually customized training plan and the adaptive difficulty level will be tailored to the user’s needs. NeuroNation MED contains over 35 multimodal exercises that target the domains of memory, attention, processing speed, and reasoning. The neurocognitive training will be continued after discharge from inpatient treatment. This is made possible because NeuroNation MED is carried out on a smartphone.**Psychotherapy** Our therapeutic approach is characterized by a permanent validation of the psychological symptoms resulting from a somatic illness, in this case, SARS-CoV-2 infection, acceptance of the status quo and at the same time strengthening self-efficacy and resource orientation. The focus of our psychotherapy concept is on developing an understanding of PASC from a biopsychosocial perspective and learning functional coping skills, taking into account the physical, psychological, and social challenges of PASC. The treatment is based on established, effective methods of cognitive behavioral therapy (CBT) and acceptance and commitment therapy (ACT). To avoid post-exertional malaise (PEM) the focus of psychoeducation is on learning the 3P principle [46], including pacing, planning, and prioritizing. Pacing means, for example, dividing tasks and activities into smaller sections throughout the day and taking breaks. Planning refers to the scheduling of support and the prior provision of aids for activities while prioritizing means setting realistic goals and assessing the importance and necessity of various tasks [2]. To ensure pacing, therapies are individually tailored, meaning patients will be allowed to skip therapies at any time as required or cancel them early. This serves as a training ground for recognizing and setting one’s boundaries.**Physical therapy** will take place in close cooperation and coordination with the Department of Physical and Rehabilitative Medicine at the Universitätsklinikum Erlangen. There will be weekly interdisciplinary meetings to discuss the patient’s current status. The so-called CoFit Training Group (e.g. circuit training, stretching exercises, balance training, breathing therapy, back exercises, etc.) will take place in a group setting twice a week for 30 min each. When indicated, patients will also receive additional pulse-controlled ergometer training in a group setting, depending on their fitness level. Our physiotherapeutic treatment concept for post-COVID will take up established physiotherapeutic treatment approaches for fatigue (e.g. for multiple sclerosis) [33, 34] and will include pacing as a central technique in all therapies. Additionally, patients will rate their symptoms and their exertion rate on the Borg breathlessness scale [47]. This ensures that individual resilience will be taken into account in the CoFit training group and ergometer training and that physiotherapy will continuously be adapted to individual’s progress.

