### Outcomes

#### Primary outcome

The primary outcome are symptoms of PASC at the end of the treatment (T1, see Table 1). To measure those, we will use the PCS-Score. The PCS-Score consists of 12 yes/no questions and covers the entire spectrum of possible PASC symptoms. Each question is given its weighting factor, which assigns a meaning to the corresponding symptom complex. The resulting sum score ranges from 0 (= complete absence of any symptoms) to 59 (= presence of symptoms in each of the 12 symptom complexes). A clinically relevant PASC can be assumed from a PCS Score of 26.25 (high PCS Score). Values between 10.75 and 26.25 indicate an intermediate or moderate PASC. The PCS Score was validated on a German population [48].

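### Controls are excluded for PASC-specific psychotherapy or psychosomatic rehabilitation used after baseline, which selects one arm on later behaviour and narrows the TAU comparator

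*Protocol article*

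**What the plan says.** The Exclusion criteria of the protocol article end with a rule for one arm: "Control group: utilization of PASC-specific outpatient or inpatient psychotherapeutic treatment or psychosomatic rehabilitation during 5 weeks of treatment". The intervention group has no corresponding rule about behaviour after baseline.

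The Control group section says that TAU participants have no access to the study's inpatient programme but "will not be restrained from using any form of care for PASC-related symptoms". It lists what TAU can entail: contacts with the treating physician or general practitioner, and "physical training, occupational therapy, or rehabilitation". It adds: "At T0, T1, and T2, participants of the control group will be questioned about the received psychotherapeutic inpatient or outpatient treatment".

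On timing, the eligibility and recruitment section states: "After detailed information and consent, eligible patients will be allocated to either a control or intervention group". Study design places the control group's T1 five weeks after T0 and its T2 six months after T0. The primary outcome is the PCS Score at T1. The primary hypothesis is superiority to TAU after treatment and at 6 months.

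**The concern.** An exclusion criterion should be decidable when the patient is enrolled. This one refers to care taken up after T0, so a control can enter the trial validly and then fail the criterion because of something done later. Use of psychotherapy in those weeks plausibly goes with outcome. The Introduction itself reports that outpatient cognitive behavioural treatment improved fatigue and coping in PASC, and that inpatient rehabilitation with psychotherapeutic elements reduced psychological and somatic symptoms. Patients who seek such care may also be more distressed or more motivated than those who do not.

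Two things are at stake. One is the validity of the primary contrast, because only one arm is filtered on later behaviour. The other is its meaning, because the filtered arm is no longer the TAU that the hypothesis names.

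**Working it through.** **Step 1: when the rule can be applied.**
- Consent, eligibility and allocation come first (eligibility and recruitment section).
- T0 follows. For controls the next assessment, T1, is five weeks later (Study design), so the 5 weeks in the criterion are the interval from T0 to T1.
- Table 1 asks controls about PASC-specific psychotherapeutic treatment at T0, T1 and T2, and about other PASC-specific treatments at T1 and T2. The T1 items are marked as control group only.
- Use within the window is therefore known only at about T1, together with the primary outcome.

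**Step 2: which comparator results.**
- Control group section: any form of care is open to controls, and rehabilitation is listed without qualification.
- Exclusion criteria: controls who use PASC-specific psychotherapy or psychosomatic rehabilitation in the window are out.
- Left in: TAU patients who used neither in those weeks. Physician contacts, physical training, occupational therapy and other rehabilitation remain allowed.
- The window ends at T1, while the hypothesis also covers 6 months. A control who starts psychotherapy in week 4 is excluded; one who starts in week 6 stays and contributes to T2.

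**Step 3: the plan's own figure.** Inputs from the sample size section: f = 0.25, correlation 0.5, power 85%, two-sided 0.05, N = 98. The between-group test in a repeated-measures ANOVA with m = 3 occasions has noncentrality

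λ = f² · N · m / (1 + (m − 1)ρ) = 0.0625 × 98 × 3 / 2 = 9.19,

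with 1 and 96 degrees of freedom. Power is 0.851, so 98 is reproduced. For two equal groups d = 2f = 0.5. The calculation contains no term for controls lost through the exclusion rule.

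**Step 4: size of a possible bias (illustration).** Let p be the share of controls removed, and δ the mean T0-T1 change of users minus that of non-users. Then

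mean change of all controls = (1 − p) · non-user mean + p · user mean,

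retained minus all = −p · δ.

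The article gives neither p nor δ; both are assumed. With correlation 0.5 the SD of change is SD × √(2 − 2 × 0.5) = 1 SD of the score, so the units agree.

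| p (assumed) | absolute δ (assumed) | Shift | Relative to d = 0.5 |
|---|---|---|---|
| 5% | 0.5 SD | 0.025 SD | 5% |
| 10% | 0.5 SD | 0.05 SD | 10% |
| 25% | 0.5 SD | 0.125 SD | 25% |

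A lower PCS Score is better. If users improved more than non-users, removing them favours the intervention. If they improved less, it works against it. A difference in level that is the same at T0 and T1 cancels in the condition-by-time test and adds nothing.

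**Step 5: numbers.** Of 58 controls, 10% is 5.8 and 25% is 14.5. The 20% dropout allowance is 11.6 of 58 and leaves 58 × 0.8 = 46.4, already below the required 49. If exclusions came on top of the full 20% dropout, the Step 3 calculation (N replaced by 4·n₁n₂/(n₁ + n₂) in λ) gives power 0.831 with none excluded, and 0.821, 0.810, 0.785 and 0.753 with 5, 10, 20 and 30% of remaining controls excluded. These shares too are assumed.

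**The case against.** The strongest reply is that keeping a close substitute for the tested treatment out of the comparator is a recognisable design choice, and that the rule is narrow. It covers only PASC-specific psychotherapy and psychosomatic rehabilitation. A reader might infer that all psychotherapy or all rehabilitation is barred; the wording does not support that. A reader might also see a flat contradiction with a TAU defined as any care. The Control group section is looser: controls are not held back from care, and psychotherapy is absent from its list of what TAU can entail. A patient can be free to seek care and still not count in the comparison. This softens the clash to the open phrase on care and the unqualified word rehabilitation. It does not remove the selection on post-baseline behaviour.

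The article also does not say whether such a control is dropped from analysis, replaced, counted as a dropout or only flagged. It follows that one cannot assert that the dropout allowance is exceeded: about 6 cases would fit within 11.6 if counted as dropout and other attrition were low. The full protocol or an SAP may settle the handling. An exclusion criterion taken at its word, however, means that the patient is not in the comparison.

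Intervention patients "patients will be allowed to skip therapies at any time as required or cancel them early", and it is tempting to present this as the mirror image. It is a weak counterpart: skipping sessions is part of the pacing concept, and the patient still receives the programme. The asymmetry rests simply on the absence of any post-baseline exclusion in that arm.

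Finally, the groups are already self-selected, and Strengths and limitations says so. That is true, but the rule adds a second source of selection which that section does not mention and which can be avoided.

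**Conclusion.** The point holds in this form. The criterion selects the control arm alone on behaviour between T0 and T1, is ascertained at about the time of the primary outcome, and turns the comparator into TAU without PASC-specific psychotherapy or psychosomatic rehabilitation. That is not TAU as the primary hypothesis states it, and the Exclusion criteria and Control group sections do not fit together.

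The size is not established. The 0.05 to 0.125 SD range rests on assumed uptake of 10 to 25% and an assumed 0.5 SD difference in change. Few patients may start such care within five weeks, and the shift would then be smaller. A reader might infer that the rule favours the intervention. The article does not support a direction: those removed may have improved through treatment, or may have sought it because they were doing worse. The loss of power is likewise conditional on how excluded controls are counted.

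The conclusion on selection and on the comparator needs none of these assumptions. It needs only that the rule is followed as written.

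**What to change.** - Reconcile the Exclusion criteria with the Control group section, so that one description of TAU applies.
- Keep all enrolled controls in the primary comparison, whatever care they used after T0.
- Report their use of psychotherapy and rehabilitation from the items already scheduled at T1 and T2 (assuming that the item on PASC-specific treatments captures rehabilitation).
- Show the analysis without users as a labelled sensitivity analysis.
- If an eligibility rule on such care is wanted, apply it only to what is known at T0. Psychotherapeutic treatment is already asked then; psychosomatic rehabilitation may need an added question.

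The cost is a change of eligibility wording and one extra analysis. The change concerns who is analysed. The downside is that the primary contrast is then against TAU including such care, which may be smaller or larger than the contrast without it.

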### Control group

The control group will consist of PASC patients for whom there is an indication for inpatient psychosomatic treatment (depressive symptoms in self-assessment: PHQ-9 ≥ 10), but who do not take up the treatment. After group allocation, participants in the TAU condition will have no access to the inpatient psychosomatic treatment, but will not be restrained from using any form of care for PASC-related symptoms. Treatment as usual for PASC patients can entail follow-up contacts with their treating physician or general practitioner, physical training, occupational therapy, or rehabilitation. At T0, T1, and T2, participants of the control group will be questioned about the received psychotherapeutic inpatient or outpatient treatment.

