**Methods and analysis:**

This study presents a non-randomized controlled trial aimed at evaluating the effectiveness of a five-week multimodal inpatient psychosomatic treatment program for individuals experiencing PASC symptoms and comorbid mental illness. A total of 118 patients presented at the Post-COVID Center at the Universitätsklinikum Erlangen will be assigned to the intervention group receiving inpatient psychosomatic treatment or the control group receiving treatment as usual. The inclusion criteria for the intervention group are a diagnosis of PASC and at least one condition of mental distress and problems with coping with illness. The primary objective of the intervention is to reduce mental ailments, including depression and anxiety, as well as neurocognitive deficits, and to address PASC symptoms such as fatigue and pain. The core elements of the treatment are psychotherapy in individual and group settings, medical treatment, neurocognitive training, and physical therapy, adapted to the individual’s capacity and oriented towards the concept of pacing. After enrollment, participants will undergo a 6-month follow-up to assess long-term results and the sustainability of the intervention effects.

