**Discussion:**

This study examines the effectiveness of inpatient psychotherapeutic treatment in PASC patients with comorbid mental illness in comparison with a control group based on treatment as usual. The results of the study can contribute to the development of evidence-based interventions to address the complex needs of patients with PASC and comorbid mental illness.

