### Objectives and hypothesis

The objective of the proposed trial is to address PASC symptoms and provide an effective treatment for PASC patients with accompanying mental illness. We aim to assess the effectiveness of a five-week inpatient treatment in the Department of Psychosomatic Medicine and Psychotherapy at Universitätsklinikum Erlangen.

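### The indication for inpatient treatment is defined differently in the two groups, so controls are not ensured to be PASC patients with comorbid mental illness, and treated patients with PHQ-9 below 10 have no counterpart

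*Protocol article*

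**What the plan says.** The Inclusion criteria of the protocol article give a common core (adult age, confirmed infection with subsequent PASC, consent, sufficient German) and then one item for each group.

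- **Treatment group:** an indication for inpatient psychosomatic treatment, supported by three entries: "Diagnosis of mental disorder (ICD-10; International Classification of Diseases, 10th Revision"), "Limitations that significantly reduce the ability to manage everyday life", and, joined by and/or, "Subjective stress so great that the quality of life and everyday resilience are significantly limited".
- **Control group:** "Control group: depressive symptoms in self-assessment (PHQ-9 ≥ 10").

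The Control group section calls the control criterion by the same name and puts the PHQ-9 score in brackets as its content. Its controls are patients with "an indication for inpatient psychosomatic treatment (depressive symptoms in self-assessment: PHQ-9 ≥ 10), but who do not take up the treatment".

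The stated target is narrower than the control criterion. The Objectives section aims to "provide an effective treatment for PASC patients with accompanying mental illness", and the abstract's Discussion announces a test of the "effectiveness of inpatient psychotherapeutic treatment in PASC patients with comorbid mental illness in comparison with a control group based on treatment as usual".

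Under Participant's eligibility and recruitment, all study patients receive interdisciplinary diagnostics at the Post-COVID Center. Table 1 schedules the PHQ-9 at T0 in both groups. The primary analysis is a mixed ANOVA with condition, time (T0, T1) and their interaction.

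**The concern.** In a non-randomized comparison the eligibility rules are the first means of making the groups alike. Here they pull the groups apart in two directions.

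1. A control needs no mental disorder, impairment or distress finding, only a self-rated score. Some controls may lie outside the population to which the conclusion is meant to apply.
2. A treated patient needs no minimum PHQ-9. Someone with, for example, an anxiety disorder and a score below 10 can enter the treatment group but not the control group. For such patients a covariate-adjusted estimate is extrapolation.

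If the PCS Score changes differently over five weeks in patients with and without a diagnosed disorder, or at low and high depression scores, that difference is counted as treatment effect. The condition-by-time interaction removes a stable difference in level between the groups. It does not remove a difference in course.

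**Working it through.** **Step 1. The criteria side by side.**

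| Requirement | Treatment group | Control group |
|---|---|---|
| ICD-10 mental disorder | named as basis of the indication | not required |
| Everyday limitations and/or severe subjective stress | named as basis of the indication | not required |
| Self-rated PHQ-9 of at least 10 | not required | required |

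The list is run together in the extracted text, so the nesting of the treatment-group entries is uncertain. The abstract is also looser: besides PASC it asks treated patients only for some form of mental distress together with coping difficulties. The asymmetry does not depend on the parse: on every reading no control needs a diagnosis and no treated patient needs a PHQ-9 of 10.

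**Step 2. Does another section close the gap?** The shared diagnostics produce information on both groups, but no section turns it into an entry requirement for controls. The Strengths and limitations section names patient choice as the source of possible imbalance and does not mention the unequal criteria. The primary ANOVA lists no term for diagnosis or baseline depression. The regression analyses for predictors are described as additional.

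**Step 3. The plan's own sample size.** Inputs from the sample size section: f = 0.25, correlation 0.5, power 85%, two-sided 0.05. For the between-group test with m repeated measurements, λ = f² × N × m / (1 + (m − 1) × 0.5). With N = 98 and m = 3, λ = 0.0625 × 98 × 3 / 2 = 9.19. With 1 and 96 degrees of freedom the power is 0.851, so the stated 98 (49 per group) reproduces. Only n = 49 and the 0.05 level are carried into Step 4.

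**Step 4. Illustration of bias under no treatment effect.** The SD of a T0–T1 change, in units of the PCS Score SD, is √(2 × (1 − 0.5)) = 1. The standard error of the difference in mean change is √(2/49) = 0.202. Let b be the shift in that difference caused by unequal selection alone. One way to build b is q × δ, where q is the share of controls without a disorder and δ is the difference in their PCS change in SD units. The documents give neither, so both are assumed. For example, 0.2 × 0.25 = 0.05 and 0.3 × 0.5 = 0.15. The noncentrality is b / 0.202, and the two-sided critical value of t with 96 degrees of freedom is 1.985.

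| Assumed b (SD) | Noncentrality | Chance of p < 0.05 with no effect |
|---|---|---|
| 0 | 0 | 5.0% |
| 0.05 | 0.247 | 5.7% |
| 0.10 | 0.495 | 7.8% |
| 0.15 | 0.742 | 11.4% |

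This covers the first mismatch only. The second would need the share of treated patients scoring below 10, which is also not given.

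**The case against.** The best reply is that the control criterion is a research threshold laid on top of a clinical assessment. All study patients go through the centre's diagnostics. The limitations paragraph says these secure a significant level of psychological distress and suitability for psychosomatic treatment. The ICD-coded exclusions are not confined to one group. Controls are described as not taking up the treatment, and allocation as a matter of patient choice.

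Much of this stands, and it rules out three stronger readings.

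- **That controls are not the objective's population.** Many patients with a PHQ-9 of at least 10 may have a depressive disorder. The text supports only that this is not ensured.
- **That some controls could never have been offered the treatment.** The Control group section and the limitations paragraph imply the opposite.
- **That a definite loss of power follows.** On the T0–T1 change contrast with d = 2f = 0.5, base power is 69%, and an adverse bias of 0.15 SD would take it to 40%. That 69% is not the plan's 85%. If f is read by the within-between convention with two measurements, power at N = 98 is 0.998. The loss depends on the mapping chosen and on assumed values of q and δ, so it is not put forward here.

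It is also fair that the limitations paragraph already allows for differences in motivation and severity. But that concession attributes them to patients' choice. Unequal entry rules come from the protocol itself and can be changed.

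**Conclusion.** The point holds in this form: the same term carries two criteria, the comparator is not ensured to match the population of the objective, and part of the treatment group may have no counterpart among controls. This rests on the eligibility text alone and is independent of the illustration.

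The size and direction of the bias cannot be derived from the documents. The range of about 6% to 11% false positives shows only what a bias of 0.05 to 0.15 SD would do with 49 per group and a correlation of 0.5. Any confounder of that size would do the same. Nothing in the documents shows that PCS change differs by diagnosis. The case for acting is that following the plan as written builds in an avoidable difference between the arms, and the data needed to reduce it are largely collected already.

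**What to change.** 1. **Reconcile the Inclusion criteria with the Control group section** so that one definition of indication applies to both groups. Its clinical content is for the investigators to settle; the statistical requirement is that it be identical. Draw it from the diagnostics that all study patients already receive, and record diagnosis status for controls.
2. **Pre-specify an added comparison** restricted to patients with a PHQ-9 of at least 10 at T0 in both groups and, where available, a documented mental disorder in both. Report treated patients below 10 separately, as uncontrolled results. This should not silently replace the full comparison, because treated patients below 10 still belong to the objective's population.
3. **If diagnoses are not available for controls,** base the controlled conclusion on the restricted comparison and word it as applying to PASC with depressive symptoms, not PASC with comorbid mental illness.

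Cost: amended wording, one recorded item for controls and a smaller comparison set. If restriction left 40 per group instead of 49, the standard error would rise by √(49/40) = 1.11, about 11%; with 35 per group, by √(49/35) = 1.18, about 18%. Both group sizes are assumptions. According to the Study design section, control T0 falls around 6 months after presentation, so diagnoses from the centre's work-up may be that old at T0, and their date should be reported. None of this removes self-selection by patient choice.
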